[23,24]. Therefore, using a telehealth approach to address the reciprocal relationship between MS fatigue and inactivity could increase the intervention’s accessibility and dissemination.

The objective of this proposed study is to conduct a RCT to examine the effectiveness of a telehealth intervention that supports individuals in managing fatigue and increasing physical activity levels. The proposed study is novel in that it represents a multi-disciplinary effort to merge two promising lines of research on MS: fatigue management and physical activity promotion. The proposed fatigue management plus physical activity intervention (FM+) will consist of incorporating a teleconference fatigue management intervention informed by the work of Packer et al.
[25], Finlayson et al.
[10], and Mathiowetz et al.
[26] with a novel, yet simple approach to promote lifestyle physical activity, i.e., encouraging goal-setting and self-monitoring with a pedometer. Our goal is to recruit 189 ambulatory individuals with MS who will be randomized into one of three telehealth interventions: (1) a contact-control social support intervention, (2) a physical activity-only intervention, and (3) a FM + intervention. Below we outline the aims, outcome measures, and associated hypotheses of the study.

### Specific aim 1

The first aim is to compare the effects of the three interventions on fatigue impact and physical activity levels. Outcomes will be the Fatigue Impact Scale (FIS)
[27], the Godin Leisure-Time Exercise Questionnaire (GLTEQ)
[28], and Actigraph accelerometers. Our hypothesis is that, in comparison to the contact-control condition, both interventions will yield significant improvements in FIS scores and physical activity levels, with the FM+ yielding significantly larger improvements.

### Specific aim 2

The second aim is to compare the effects of the three interventions on health-related quality of life, mental health, and participation in life roles. Outcomes will be the SF-12, Mental Health Inventory (MHI), Multiple Sclerosis Impact Scale (MSIS)
[29,30], and the Community Participation Indicator (CPI)
[31,32]. Our hypothesis is that, in comparison to the contact-control condition, both interventions will yield a significant increase in SF-12, MHI, MSIS, and CPI scores, with the FM + yielding a significantly larger increase.

### Specific aim 3

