### Sample size

In order to achieve an adequate power of 0.80 to test hypotheses, we will seek to recruit a total of 189 individuals for this study and, more specifically, 63 in each condition. The total number of individuals to be recruited is based on calculations of sample size and power for a balanced repeated-measure mixed effect model with three time points (Weeks 1, 12, and 24) using a formula provided by Hedeker et al.
[33]. We assumed equal variance and correlation (rho = 0.5) between measures across time points, and an effect size of 0.6 at Weeks 12 and 24. These calculations account for 20% attrition over time.

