### Recruitment and eligibility

Individuals for this study will be recruited in several different ways in the State of Ohio. We have restricted recruitment to Ohio to avoid complications with state licensure laws. Fliers for the study will be distributed through MS support groups and National MS Society and MS Association of America events. We will recruit through physician referral and electronic health record review, and an MS patient registry maintained by the North American Research Consortium on MS (NARCOMS), which has approximately 400 registered individuals in Ohio who are ambulatory. Regardless of the recruitment method, individuals who are interested in participating in the study will be asked to contact the study office. Potential participants will undergo a telephone screening procedure to determine eligibility, and then a confirmation of eligibility through contacting their physician.

Inclusion criteria are: (1) physician-confirmed diagnosis of MS and physician-consent to initiate a physical activity program, (2) age between 18 and 65 years, (3) ability to walk at least 25 feet with a cane, (4) ability to carry on telephone conservations in English, (5) a Patient Determined Disease Step score between 1 (mild disability) and 5 (unilateral support required)
[34], (6) a current sedentary lifestyle (i.e., purposeful exercises ≤ 2 days per week for 30 minutes)
[35], and (7) experiences moderate to severe fatigue (a score of ≥ 4 on the Fatigue Severity Scale)
[36]. Exclusion criteria are: (1) pregnancy, (2) cardiopulmonary diseases, (3) uncontrolled diabetes (hospitalized within the last six months), (4) greater than three falls in the past six months, and (5) severe cognitive deficits (weighted score of less than 12 on the short version of the Blessed Orientation Memory Concentration test)
[37].

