##### Data management and analysis

A secure online application, Research Electronic Data Capture
[49], will be used to manage recruitment efforts and facilitate data collection. The first step in the analysis process will be to compute summary statistics, calculate outcome scores, and conduct quality control assessments. The second step in the analysis will be to test whether the randomization process resulted in equivalent groups at baseline. If differences are found at baseline, these variables will be used as covariates during the hypothesis testing phase. The third step in the analysis process will be addressing normality assumptions, and the potential for missing data, before hypothesis testing begins. If the normality assumption is violated, then an appropriate data transformation will be used. Missing data will be treated conservatively. If appropriate, maximum likelihood, multiple imputation, or last observation carried forward will be used to estimate the missing values. After addressing issues of attrition and missing data, the fourth step will be to conduct intent-to-treat analysis to test the hypotheses. Linear mixed-effects models will be used as the primary analysis tool for testing hypotheses, which include condition, time, and interactions as the fixed covariates, and a random intercept that models the correlation among outcomes collected from the same subject. The mixed models will allow us to determine whether there are significant differences between the three conditions and whether there are significant differences across time. All tests will be two-sided, and p = 0.05 will serve as the criterion for significance. As is typically the case for mixed-effects analyses, the results will not be controlled for multiple comparisons. The generalized estimating equation approaches will be used if the normality distributional assumption is violated for the random effects in the mixed models. To test for mediation, we will use a linear regression model. This analysis will first involve regressing changes in fatigue impact or physical activity on the intervention conditions, and then regressing changes in fatigue or physical activity on the intervention conditions plus changes in the potential mediator. Mediation will be based on the interventions’ association with physical activity or fatigue impact being reduced in magnitude and non-significant after controlling for the mediator variable.

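### The stated inference names condition and time differences, not the condition-by-time contrast that the hypotheses need; naming that contrast and fixing the baseline adjustment costs nothing and adds power

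*Protocol article*

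**What the plan says.** Under Data management and analysis, linear mixed-effects models are the main tool for hypothesis testing. Their fixed effects are condition, time and interactions, with a random intercept per participant. The one sentence on what will be read from the models says they will show "whether there are significant differences between the three conditions and whether there are significant differences across time". Variables found to differ between arms at baseline become covariates; otherwise no baseline adjustment is stated. On error rates: "All tests will be two-sided, and p = 0.05 will serve as the criterion for significance", and "the results will not be controlled for multiple comparisons".

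Under Sample size, the model has three time points (Weeks 1, 12 and 24), equal variances, a correlation of 0.5, "an effect size of 0.6 at Weeks 12 and 24", and an allowance for 20% attrition. The target is to "recruit a total of 189 individuals for this study and, more specifically, 63 in each condition".

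Under Specific aim 1 (Background), both active arms are expected to improve relative to the contact control, "with the FM+ yielding significantly larger improvements".

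**The concern.** The hypotheses ask whether one arm improves more than another. With Week 1 as an outcome, that is a between-arm difference in change: a condition-by-time contrast. Neither of the two effects named in the inference sentence is that contrast.

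- **Condition effect averaged over visits.** It includes Week 1, where randomisation makes the expected difference zero, so the effect is diluted.
- **Condition coefficient under reference coding, with interactions in the model and Week 1 as reference.** It is the baseline difference, whose true value is zero. It says nothing about treatment.
- **Time effect.** It is not a between-arm comparison. Entry requires "a score of ≥ 4 on the Fatigue Severity Scale" and a sedentary lifestyle, so some movement toward the mean may occur in every arm. The documents give no figure for its size.

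At stake are the power of the test actually used and the freedom to choose the decisive term after the results are seen.

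**Working it through.** **Inputs.** From Sample size: 63 per arm, effect 0.6 SD at Weeks 12 and 24 (so 0 at Week 1), rho = 0.5 between all visits, 20% attrition. From Data management and analysis: two-sided 0.05, no multiplicity adjustment. After attrition, 63 × 0.8 = 50.4, taken as 50 per arm. The article does not say which pair of arms differs by 0.6; the pairwise figures hold for any pair that does.

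**Formulas.** Power = Φ(δ / (SD × √(2/n)) − 1.96). Sample size per arm = 2 × (1.96 + 0.8416)² × SD² / δ², divided by 0.8 for attrition.

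**The plan's own figure (63 per arm for power 0.80).**
- Change to one visit: 2 × 7.849 × 1 / 0.36 = 43.6, so 44, and 44/0.8 = 55.
- Mean of Weeks 12 and 24 minus baseline: 2 × 7.849 × 0.75 / 0.36 = 32.7, so 33, and 33/0.8 gives 42.
- Condition effect averaged over three visits: 2 × 7.849 × 0.6667 / 0.16 = 65.4, so 66, and 66/0.8 gives 83.

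None of these is 63. A 4-df condition-by-time test with arms at 0, 0.3 and 0.6 SD needs 50 per arm, and 50/0.8 gives 63. That arm pattern is an assumption of this check; the article does not state it.

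**If the averaged condition effect were the test.**
- Effect: (0 + 0.6 + 0.6)/3 = 0.4 SD.
- SD of a three-visit mean: √((1 + 2 × 0.5)/3) = 0.8165.
- n = 50: 0.4 / (0.8165 × √(2/50)) = 2.449; power 68.8%.
- n = 63, no attrition: power 78.5%.
- Likelihood analysis keeping dropouts' observed data: 75.2% (80% retained at both later visits) to 76.4% (90%, then 80%).
- Sensitivity to rho, n = 50: 78.2% at rho 0.3, 57.5% at rho 0.8. With rho 0.3 and no attrition it is 86.7%, so the shortfall is not universal outside the plan's own rho.

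**If the condition-by-time contrast is the test (n = 50).**
- Change to one visit: variance 2(1 − 0.5) = 1; 0.6 / (1 × 0.2) = 3.0; power 85.1%.
- Two-visit mean minus baseline: variance 0.75 + 1 − 2 × 0.5 = 0.75; 0.6 / (0.866 × 0.2) = 3.464; power 93.4%.

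**The same contrasts with baseline means constrained equal (or baseline as covariate).**
- One visit: variance 1 − 0.5² = 0.75, again 3.464; power 93.4%.
- Two-visit mean: variance 0.75 − 0.5² = 0.50; 0.6 / (0.7071 × 0.2) = 4.243; power 98.9%.

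With 50.4 in place of 50 per arm, the averaged condition effect has 69.1% and the 93.4% figures become 93.5%.

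**The case against.** A reader might infer that the plan decides its hypotheses on main effects and that the trial therefore has 69% power. The documents do not support this. Interactions are among the fixed effects of the model assigned to hypothesis testing. The inference sentence describes what the models can show and names no coefficient, and differences between conditions can be read as including between-arm contrasts at Weeks 12 and 24. The hypotheses are comparative, so a time effect shared by all arms would not satisfy them. An effect assumed only at Weeks 12 and 24 is itself a condition-by-time pattern, and 63 per arm is well short of the 83 that a pairwise averaged-condition test would need. All of this stands.

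The 69% is also the low end at the plan's rho. It takes completers only and averaged main effects; under the reference coding described above, the dilution figure does not apply at all.

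It can further be said that an article leaves the exact contrast to a fuller plan. That is a fair limit on the point, but the article does state what will be read from the model, and that statement leaves out the quantity its hypotheses are about.

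Finally, constraining baseline means is not needed to reach 0.80, because the unconstrained contrasts already exceed it. That is true; it is offered as a free gain.

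**Conclusion.** The point holds as an ambiguity with a costless improvement. The stated inference does not name the condition-by-time contrast, and it leaves open readings that do not test the hypotheses. Under the plan's rho of 0.5, reading the averaged condition effect would put pairwise power at about 69% to 79%, below the target in "In order to achieve an adequate power of 0.80 to test hypotheses". Reading the condition-by-time contrast gives about 85% to 93%, above it. Nothing here shows that the trial is underpowered or that 63 per arm is wrong: 63 exceeds the 55 needed for a pairwise change contrast, and the contrast behind it is not given. The figures rest on equal variances, equal correlation, a true pairwise difference of 0.6 SD at both later visits and, except where stated, 50 completers per arm.

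**What to change.** Replace the inference sentence with one or two that say:

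- Each hypothesis is tested by the pairwise between-arm contrast at Week 12 and at Week 24, or by their average, with the choice fixed in advance.
- The baseline mean is constrained equal across arms, or the baseline value of the outcome is always a covariate, whether or not a baseline difference is observed.
- Condition and time main effects are descriptive.

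The cost is wording only. The baseline values are already collected, and neither the sample size nor the schedule changes. With about 50 per arm, the baseline step lifts power from about 0.85 to 0.93 at one visit and from about 0.93 to 0.99 for the two-visit average.

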##### Primary dependent variables

All dependent variables will be administered at baseline, at the end of the 12-week intervention period, and at a 24-week follow-up period through the mail.

Fatigue impact will be measured using the Fatigue Impact Scale
[27]. This 40-item scale evaluates the perceived impact of fatigue on everyday life, and is valid and reliable among people with MS. It was developed by interviewing patients with MS, and has discriminant validity between patients with MS, general fatigue, and essential hypertension
[27]. Respondents rate each statement using a five-point Likert-type scale ranging from 0 (no problem) to 4 (extreme problem). A total score and three subscale scores (physical, social, cognitive) can be produced from participants responses. The FIS was used to detect changes in fatigue impact resulting from a fatigue management teleconference program
[10].

Physical activity will be evaluated using the Godin Leisure-Time Exercise Questionnaire (GLTEQ)
[28] and an Actigraph tri-axis accelerometer. The GLTEQ is a self-administered measure of usual physical activity. The GLTEQ includes three items that measure the frequency of strenuous, moderate, and mild exercise for periods of more than 15 minutes during one’s free time in a typical week. Participants will be sent an accelerometer to wear daily over three seven-day periods (baseline, post-test, and follow-up). Data are retrieved for analysis via a computer and software provided with the unit. We will use an epoch of one minute. Participants will be instructed to wear the accelerometers all day, except while showering and swimming, for each of the three seven-day measurement periods. The participant will use a log to record the time that the accelerometer is worn, and this will be verified by inspection of the minute-by-minute accelerometer data. Motl et al. have demonstrated the validity and reliability of both the GLTEQ and the accelerometer in the population with MS
[42].

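### The Aim 3 mediation regressions use raw change scores without the baseline values already collected, which costs about 8 points of power on the step-1 total effect at the plan's own inputs

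*Protocol article*

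**What the plan says.** The mediation analysis stands apart from the linear mixed model used for the main hypotheses. Under Data management and analysis, the first step is described so: "This analysis will first involve regressing changes in fatigue impact or physical activity on the intervention conditions". The second step is "then regressing changes in fatigue or physical activity on the intervention conditions plus changes in the potential mediator". Mediation is declared if the condition effect shrinks and is no longer significant once the mediator change is in the model.

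No baseline term is named in either step. Yet under Primary dependent variables the article says: "All dependent variables will be administered at baseline, at the end of the 12-week intervention period, and at a 24-week follow-up period". The psychosocial measures proposed as mediators are listed under Secondary dependent variables, so they fall under the same schedule.

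The only stated rule that would bring a baseline variable into a model is conditional: the arms are tested at baseline, and variables that differ become covariates in the hypothesis tests.

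**The concern.** A change score subtracts the whole baseline value, which amounts to fixing the baseline coefficient at 1. With equal variances and a correlation of 0.5 between visits, the coefficient that minimises residual variance is 0.5. The raw change score therefore over-corrects for chance baseline imbalance and carries variance that a covariate would remove.

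The conditional rule does not repair this. Under randomisation, a 5% baseline test flags any one variable about once in 20 times, so in most cases no adjustment would be made, and whether it is made would depend on the data.

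At stake is the precision of the step-1 total effect, the quantity that a mediator is meant to explain. Aim 1 is tested by the mixed model and is not affected.

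**Working it through.** **Inputs** (Sample size section unless noted)
- Effect: "an effect size of 0.6 at Weeks 12 and 24", read as SD units of a single measurement.
- Correlation: "We assumed equal variance and correlation (rho = 0.5) between measures across time points".
- Numbers: "we will seek to recruit a total of 189 individuals for this study and, more specifically, 63 in each condition". With the stated 20% attrition, 63 × 0.8 = 50.4, so about 50 evaluable per arm.
- Test level (Data management and analysis): "All tests will be two-sided, and p = 0.05 will serve as the criterion for significance", so z = 1.96.

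**1. The plan's own figure.** The target is introduced with "In order to achieve an adequate power of 0.80 to test hypotheses". The plain two-mean formula gives 2 × (1.96 + 0.84)² / 0.6² = 43.6, so 44 evaluable per arm; 44 / 0.8 = 55 enrolled, or 165 in total. A contrast of baseline with the mean of the two follow-ups gives 33 evaluable, or 41 enrolled. Neither gives 63, so the stated size is not reproduced; it exceeds both. This does not affect the point, which uses 63 only as the number enrolled.

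**2. Residual variance of the step-1 model**, with the SD at each visit set to 1:
- Change score on condition: 2(1 − ρ) = 2(1 − 0.5) = 1.00.
- Baseline outcome added: 1 − ρ² = 1 − 0.25 = 0.75, a cut of 25%.

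**3. Power for one arm contrast at one follow-up**, Φ(d / √(2v/n) − 1.96):
- Change score: √(2 × 1.00 / 50) = 0.200; 0.6 / 0.200 = 3.00; Φ(1.04) = 0.851.
- Baseline-adjusted: √(2 × 0.75 / 50) = 0.173; 0.6 / 0.173 = 3.46; Φ(1.50) = 0.934.
- Difference: 8.3 points.

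The noncentral t gives 84.6% against 93.1%. A three-arm simulation of 20,000 trials gives 85.1% against 93.1%.

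**4. Sensitivity.** Correlations other than 0.5 and effects other than 0.6 are assumptions.

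| ρ | d | n per arm | Change score | Adjusted | Gap (points) |
|---|---|---|---|---|---|
| 0.5 | 0.6 | 50 | 85.1% | 93.4% | 8.3 |
| 0.5 | 0.6 | 63 | 92.0% | 97.3% | 5.3 |
| 0.3 | 0.6 | 50 | 71.8% | 88.2% | 16.4 |
| 0.7 | 0.6 | 50 | 97.2% | 98.7% | 1.5 |
| 0.5 | 0.4 | 50 | 51.6% | 63.7% | 12.1 |
| 0.5 | 0.3 | 50 | 32.3% | 41.0% | 8.7 |

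**5. Does the gap reach the mediation verdict?** This needs an assumed mediator structure, because the article gives no mediator correlations. Simulations of how often mediation is declared gave:
- *Half the effect mediated, stable mediator and outcome levels correlated 0.5* (50 per arm, ρ = 0.5, total effect 0.6): 0.61 unadjusted and 0.53 adjusted under the rule as written; 0.47 and 0.46 if step 1 must also be significant.
- *Complete mediation, same set-up*: 0.94 and 0.94 as written; 0.82 and 0.89 if step 1 must be significant.
- *No true mediation, step 1 required to be significant*: false verdicts went from 0.06 to 0.13 with correlated stable levels, but from 0.19 to 0.04 with autoregressive data.

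The effect on the verdict can therefore go either way.

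**The case against.** **The article is condensed and does not forbid covariates.** It names variables for possible use as controls, and an analysis plan that is not shown may add more. That is fair as far as it goes. But the article states the response, the predictors of each step and the decision rule, and its one stated rule for baseline covariates is conditional on a difference being found. The model is fixed here, not left open.

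**The change-score model is legitimate.** Regressing change on change matches the Aim 3 hypothesis that improvement in the mediator explains the effect, and randomisation keeps the total effect unbiased. This stands: the issue is efficiency only.

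**Power of 0.85 already exceeds the planned 0.80.** True at the central inputs. It is not true at a correlation of 0.3, or for the smaller effects in the table.

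**The correlation is borrowed** from the mixed-model sample size. This stands, and it is why a range is given.

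**Two stronger readings do not hold.**
- A reader might infer that 8 points are lost on the Aim 3 conclusion. The stated rule turns on non-significance in step 2 and does not expressly require a significant step 1; the simulations show no consistent direction.
- A reader might also infer the same loss in the interventions' effect on each mediator. The article hypothesises that mediator scores improve, but states no regression of mediator on condition, so no model is fixed there to criticise.

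**Conclusion.** The point holds as a loss of efficiency in the step-1 total effect. At the plan's own inputs, leaving out the baseline outcome lowers power for one arm contrast from about 0.93 to 0.85, so the chance of missing a 0.6 SD effect rises from about 7% to 15%.

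This rests on reading 0.6 as SD units, on equal variances and a correlation of 0.5 holding for the Aim 3 outcomes, and on about 50 complete pairs per arm. The size is sensitive to the correlation, and shrinks to 1.5 points at 0.7. It comes from the baseline outcome alone; what the baseline mediator would add cannot be quantified from the article.

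The change is worth making because it is nearly free. It does not repair a mediation rule based on loss of significance.

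**What to change.** In Data management and analysis, state that both mediation regressions include the baseline value of the outcome and of the mediator as covariates for every participant, whether or not the arms differ at baseline. Use the same two terms in step 1 and step 2, so that the condition coefficients can be compared. Report the unadjusted change-score version as a sensitivity analysis.

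The cost is one sentence and two degrees of freedom out of about 150 (3 × 50) participants, with no new data. The downside is small but real: the mediator-outcome slope can move (by about 0.09 in a simulation with stable mediator and outcome levels correlated 0.5), and the step-2 verdict can shift in either direction. The sensitivity analysis would show this.

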The third aim is to identify potential mediators of the interventions. Psychosocial constructs measures related to fatigue and physical activity (e.g., self-efficacy, goal-setting, and outcome expectations) will be administered to help identify the underlying mechanisms of the interventions’ possible effectiveness. Our hypothesis is that scores on these measures will significantly improve, and that improvements will explain the interventions’ effect on fatigue and physical activity.

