##### Secondary dependent variables

Health-related quality of life, mental health, and participation in life roles will be measured with the SF-12, Mental Health Inventory, and Community Participation Indicator (CPI), respectively. The SF-12 and Mental Health Inventory are valid and reliable measures, and are commonly used in the population with MS
[43]. The CPI is a new measure developed by Heinemann and colleagues. The measure was developed with input from multiple stakeholders, and has been validated through Rasch analysis in a sample of 1,163 individuals with a variety of disabling conditions
[31,32]. In a subsequent online survey study, the measure had good test-retest reliability over a 2.5 month period in people with MS (t = 0.12, p = 0.91; r = 0.84, p < 0.01). For each item, respondents rate the frequency of engagement (either in days, hours, or times per week, depending on the type of activity), whether it was important (yes/no), and whether they were doing it not enough, enough, or too much. Examples of the 20 items included are: work for money, provide care for a loved one, volunteer, and participate in learning activities.

Six questionnaires will be implemented to identify underlying mechanisms of the interventions’ possible effectiveness for increasing physical activity levels and reducing fatigue impact. Psychosocial construct measures for physical activity will be the Self-Efficacy for Exercise Scale
[44], Exercise Goal-Setting Scale
[12,45], and Multidimensional Outcome Expectations Scale
[46]. All three questionnaires are validated and have been used in previous MS research on physical activity
[45,47]. Psychosocial construct measures for fatigue management will be the validated Self-Efficacy for Performing Energy Conservation Strategies
[48] along with two additional measures on goal-setting and outcome expectations, which will be developed and validated during the study.

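### Aim 3 declares mediation from a non-significant direct effect and never tests the indirect effect, so it loses true partial mediators as precision grows and can declare false ones

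*Protocol article*

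**What the plan says.** Under Specific aim 3 the protocol article states: "The third aim is to identify potential mediators of the interventions". The hypothesis is that scores on the psychosocial measures will improve and that these "improvements will explain the interventions’ effect on fatigue and physical activity". Under Secondary dependent variables, the candidates are set out: "Six questionnaires will be implemented to identify underlying mechanisms".

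Data management and analysis gives the method in two regressions and a criterion:

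- Step 1: "This analysis will first involve regressing changes in fatigue impact or physical activity on the intervention conditions".
- Step 2: "regressing changes in fatigue or physical activity on the intervention conditions plus changes in the potential mediator".
- Criterion: the intervention's association "being reduced in magnitude and non-significant after controlling for the mediator variable".

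The same section sets the significance level, "All tests will be two-sided, and p = 0.05 will serve as the criterion for significance", and says that "the results will not be controlled for multiple comparisons". It attaches no significance condition to step 1. It names no test or interval for either path or for the indirect effect, and it does not say which visits define the changes.

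**The concern.** The criterion has two parts: the condition coefficient must shrink, and it must not be significant. The second part treats failure to reject a null hypothesis as a finding. Whether a direct effect reaches p < 0.05 depends on its size, on the number of participants and on the overlap between condition and mediator. A mediator that carries part of the effect leaves a real direct effect behind. The more precisely the trial measures that remainder, the more surely it is significant and the mediator is rejected. Partial mediation is plausible when several questionnaires are offered as mechanisms.

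The first part is weak in the other direction. If the mediator has no link to the outcome, its estimated coefficient is still not exactly zero, and adding it moves the condition coefficient up or down by chance. A chance reduction plus a non-significant result meets the rule. Where the intervention has no effect at all, the second part is met almost automatically.

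At stake is what the trial can conclude about mechanism under Aim 3, since this criterion is the only stated basis for that conclusion.

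**Working it through.** The protocol gives no figure for the mediation analysis, so there is none to reproduce. The check asks how the stated rule behaves at about the planned size.

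**Inputs from the protocol article.** Under Sample size: 63 per arm, 20% attrition and an effect of 0.6 SD. Completers: 63 × 0.8 = 50.4, about 50 per arm. Two-sided 0.05 comes from Data management and analysis.

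**Assumptions (the document gives no path values).** Two arms, X = 0 or 1. Mediator change M = aX + error, with SD 1. Outcome change Y = c′X + bM + error, with total within-arm SD 1, so the residual variance given M is 1 − b². The total effect is c′ + ab. No unmeasured common cause of M and Y.

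**Decision rules compared.**
- As written: the condition coefficient is smaller in magnitude after M is added, and p ≥ 0.05.
- With step 1 read in: the same, and the step-1 effect is also significant.
- Joint test: a and b both significant.

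**Half-mediated effect, by hand.** Take a = 0.6, b = 0.5, c′ = 0.3, so the total is 0.3 + 0.6 × 0.5 = 0.6. With n per arm,

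SE(c′) ≈ √[(1 − b²)(2/n + a²/(2n − 2))].

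- n = 50: √[0.75 × (0.04 + 0.36/98)] = 0.181. 0.3/0.181 = 1.66. P(non-significant) ≈ Φ(1.96 − 1.66) = Φ(0.30) ≈ 0.62.
- n = 200: √[0.75 × (0.01 + 0.36/398)] = 0.090. 0.3/0.090 ≈ 3.32. Φ(1.96 − 3.32) = Φ(−1.36) ≈ 0.09.

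The coefficient nearly always shrinks here, so these approximate the rule itself. Simulation agrees:

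| n per arm | Rule as written | Joint test |
|---|---|---|
| 25 | 75% | 53% |
| 50 | 63% | about 85% |
| 100 | about 35% | 99% |
| 200 | about 10% | 100% |
| 400 | 0.3% | 100% |

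At 50 per arm the rule misses 100 − 63 = 37%. With a significant step 1 read in, it declares about 48% and misses about 52%. From 100 per arm upwards the two readings almost coincide, because the total effect is then nearly always significant.

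**No mediator-to-outcome link (b = 0), 50 per arm.**

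| a | Total effect | Rule as written | Step 1 read in | Joint test |
|---|---|---|---|---|
| 0.6 | 0.6 | about 13% | about 5% | 4% |
| 0.8 | 0.5 | about 24% | about 9% | about 5% |
| 0.6 | 0.3 | about 38% | about 5% | 4% |
| 0 | 0 | about 47% | about 0.4% | 0.2% |

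The last row can be seen by hand: the coefficient shrinks by chance about half the time and is non-significant about 95% of the time, so 0.5 × 0.95 ≈ 0.47. This does not improve with size; at 400 per arm it is still 47%. For b = 0 the joint test is bounded by P(a significant) × 0.05, for example 0.84 × 0.05 = 0.042 at a = 0.6.

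**The case against.** The best defence is that step 1 exists to establish an effect to be explained, so a significant total effect is implied. On that reading false declarations are modest, about 0.4% to 9% per mediator in the scenarios tried. A reader might go further and treat that requirement as part of the plan. The text does not support this: step 1 is described with no significance condition. The distinction matters for the figures. Full mediation of a 0.3 SD effect at 50 per arm is declared in about 29% of trials with the gate but about 77% as written, against about 85% by the joint test. The low gated figure mainly reflects power of about 32% for the total effect, not the non-significance criterion. The reading also does not rescue the rule, since detection of a half-mediator falls to about 48%.

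A reader might also infer that mediator and outcome changes are taken over the same interval, so that direction cannot be told. The document names no visits for these changes. Measures are taken at Weeks 1, 12 and 24, so ordered models are not excluded, and the choice may properly sit in the analysis plan.

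Nor do the documents show that this trial will report wrong mechanisms. Every path value above is assumed, and the results at 200 and 400 per arm illustrate the principle, not this trial's size. The simulations use two arms, while the plan regresses on three conditions.

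Specific aim 3 does hypothesise that mediator scores improve, which resembles a test of the first path. It is not part of the criterion for mediation.

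An analysis plan that is not shown does not answer the point. The protocol is not silent here: it fixes the criterion.

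**Conclusion.** The point holds. The rule is wrong as written, because it bases mediation on a non-significant direct effect and tests neither path nor the indirect effect. Two consequences follow on the literal text: true partial mediators are lost as precision grows, and mediators with no link to the outcome can be declared. On the narrower reading with a significant step 1, the second is much reduced and the first remains.

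The sizes rest on the assumed path values, two arms, within-arm SD 1 and about 50 completers per arm. The direction of the results follows from the form of the rule. The rule is meant for six candidate questionnaires with no multiplicity control, so the per-mediator false-declaration rates apply repeatedly. The defect is confined to Aim 3; the mixed-model comparisons of the primary and secondary outcomes are untouched. It should be corrected, but it does not threaten the trial's main conclusions.

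**What to change.** Replace the criterion in Data management and analysis. For each active arm versus control, estimate the indirect effect as the product of the arm-to-mediator and mediator-to-outcome paths, adjusted for the baseline mediator and baseline outcome, with a bootstrap 95% confidence interval. Declare mediation when the interval excludes zero. Remove the requirement that the direct effect be non-significant; report the direct effect with its interval, but let no verdict depend on its p-value. A model with the Week 12 mediator and the Week 24 outcome may be added as a supportive analysis.

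State with the results that randomisation does not protect the mediator-to-outcome path, so the estimate still assumes no unmeasured common cause of the two changes.

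The cost is a change of analysis wording and standard software. No new data, visits or participants are needed.
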